#### Pretrained deep learning models

It is likely that the performance of the imaging CNNs will be improved by using pretrained models and transfer learning models.^24^

#### Ensemble approaches/classical machine learning models

It is anticipated that the final classification will benefit from an ensemble approach using different AI/ML models to optimise classification. For example, decision trees, support vector machines, nearest neighbour and naive Bayes’ classifiers, all of which have been used extensively in previous radiotherapy and cancer classification problems.^25^,^31^

Serving as input data to these models will be unique information, or features, extracted from radiotherapy, imaging and EHR data. Currently, it is estimated that there will be, per time point of interest, more than 500 features of interest comprising:

Radiotherapy planning features (n=20+ features).Including, but not limited to, dose to prostate and organs at risk, organ volume, number of fractions, delivery technique, dose calculation algorithm.Image analysis/radiomic features (n=150+ features).Including texture/radiomics analysis based on low-level and high-level feature analysis, features based on organ shape and position, features derived from other approaches such as Fourier analysis and wavelet analysis.Clinical/patient-specific features from EHRs (n=431 features at multiple timepoints).Including PSA, staging, Gleason score, age, smoking history, comorbidities including prescription medications via ICD-10 indicative of diseases such as cardiovascular and diabetes.

### Computational environment

All data linkage and computation will be done within a secure virtual environment specially designed and built for the PROSECCA study by the Edinburgh Parallel Computing Centre (EPCC). This is one of the leading supercomputing centres in Europe hosting the UK’s Tier-1 research supercomputer as well as a number of other high-performance computing (HPC) systems including the Cirrus system, a national Tier-2 HPC service.^32^ The centre also hosts the first European deployment of a Cerebras CS-1 High Performance AI Computer, specifically designed to address the challenges of large-scale public health data sets. For the duration of the PROSECCA study, secure access to the data and to HPC computing resources will be available for researchers through this virtual environment. Figure 5 shows the key elements of this environment.

**Figure 5 F5:**
[figure not shown]
PROSECCA trusted research environment (TRE) showing connections from the Scottish Cancer Centres. Access is through a secure virtual private network (VPN), from where researchers can securely access the data and access a range of high-performance computing resources for rapid model development and testing. DB, database; EASE, University of Edinburgh's staff portal; GGC, Greater Glasgow and Clyde; MFT, multi-factor authentication; PI, principal investigator; RDS, Remote Desktop Connection; TBD, to be decided.

### External validation

A critically important step built in to the PROSECCA methodology is external validation. This will establish how well the model is calibrated and reacts to new unseen data and accounts for variability in the data collected from different patients, centres and at different time points. This has been taken into account by linking to Hamlet-RT, a prospective Cancer Research UK-supported study aimed at developing a way of predicting long-term side effects of radiotherapy (NCT04060706, REC 19/NE/0290).^33^ By deploying the algorithms developed on PROSECCA on the Hamlet-RT data set, it will be possible to validate performance on an independent UK-wide prostate cancer data set. In addition, all prediction models will be reported adhering to the consensus guidelines set out in Transparent Reporting of a multivariable prediction model for Individual Prognosis Or Diagnosis (TRIPOD)^34^ and as set out in the European Society for Radiotherapy and Oncology (ESTRO) position paper actively promoting this approach as part of the methodology required to bring clinical decision tools into the clinic.^35^

### Progress to date

To date, radiotherapy data from approximately 9500 patients has been collected and stored within the PROSECCA store and this will continue to grow over the coming months. However, one of the limiting factors of the study is that when radiotherapy data are removed from a clinical treatment planning system and transferred to a research environment, accessing key radiotherapy information is difficult without specialist computing skills. For example, information on the planned dose to an organ at risk from radiation, the volume of an organ receiving 95% of the total dose and the location of an organ on any day of treatment are all key parameters affecting patient response. While the current PROSECCA researchers have the necessary skills to interpret this data, it would be beneficial if a clinical treatment planning system was installed within the trusted research environment, which is planned for the future.

### Patient and public involvement

From the initial conceptualisation of the proposal, there has been patient and public involvement and engagement (PPIE). The original PPIE team offered guidance and codeveloped the submission by reviewing and providing feedback on early versions of the submission documentation. After funding was secured, two further members joined the group and have provided input through the steering committee and regular communication with the study team.

The PPIE team will continue to provide guidance and evaluate the study conduct on all levels. Their input will be particularly important as output from the study is prepared for presentation to lay audiences. One member of the PPIE team is also a past chair of a prostate support group and through this network will be able to disseminate information about the project. The team also intends to take advantage of the public engagement activities organised by Prostate Cancer UK (PCUK) to communicate the findings more widely.

### Protocol

#### Patient selection

Patients with prostate cancer who have received external beam radiotherapy with radical intent are eligible for inclusion in the PROSECCA study. Patients must have had PSA recorded at regular intervals after radiotherapy, a radiotherapy planning CT and corresponding radiotherapy and healthcare data available.

Patients who have received external beam radiotherapy as part of a palliative treatment schedule are not eligible for inclusion in the study, as well as those with no PSA information and follow-up healthcare and imaging data.

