### Prediction of a patient’s risk of radiation toxicity and tumour control

Using the linked dataset, predictive factors will be established indicating that a patient may have a poor response to treatment, including the increased risk of normal tissue toxicity. This information will be available both (1) prior to treatment and (2) during the course of treatment.Medium (5 year) and long (10 year) estimates of three clinically significant endpoints: (1) PSA relapse-free survival, (2) overall survival and (3) radiotherapy toxicity.To ensure maximum clinical impact, a software application, available to clinicians in the clinic, will be developed to use these predictive factors to identify (1) the most appropriate form of therapy, (2) the most appropriate dose and fractionation schedule and (3) the optimal time and how best to adapt treatment.To establish a pathway and methodology showing how the approach developed in PROSECCA can be applied to other tumour sites (eg, lung and head and neck cancer), thereby benefiting a much larger number of patients treated with radiotherapy.

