**Figure 2 F2:**
[figure not shown]
Graphical illustration of the radiotherapy workflow showing the inclusion of healthcare data from HSC-PBPP/PHS as proposed in the PROSECCA study. C: Here the creation of a radiotherapy plan uses significant personal information from a patient’s EHR. In addition, it will include information obtained from population-level analysis on the influence that other healthcare factors, which are documented in HSC-PBPP/PHS healthcare records, have on treatment response. D: Here, significant attention will be paid to a patient’s EHR after treatment to establish, and understand more about, the factors indicating that they may have had a poor response to treatment, or an increased risk of side effects (toxicity) from radiation. For example, it will be possible to study the protective effect that medications such as statins or antihypertensive medications have and how they may reduce radiotherapy-related toxicity.

The study aims to include complete data sets from approximately 15 000 prostate patients who received radiotherapy at one of the five Scottish cancer centres, namely Aberdeen, Dundee, Edinburgh, Inverness and Glasgow (Figure 3). This estimate was based on an initial assessment of data from NHS Scotland Information Services Division (ISD), which indicated that over the proposed timeframe approximately 25 000 patients with prostate cancer were treated with radiotherapy in Scotland. It has been assumed that 40% of data will be incomplete or not suitable for the endpoints, Prostate Specific Antigen (PSA) relapse-free survival and overall survival, and that 60% of data will be incomplete or not suitable for the endpoint radiotherapy toxicity reported from all sources. From this, for each of the three key endpoints, the expected number of significant events in the study population was estimated to be: PSA relapse-free survival=1125; overall survival=2175; radiotherapy toxicity=1200. These preliminary estimates indicate that even with this level of incomplete data, there is still a sufficient number of complete data sets available to achieve the project goals. More details on how these figures were obtained are included in table 1.

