**Figure 3 F3:**
[figure not shown]
Map showing the location of the five Scottish Cancer Centres and in brackets the number of clinical linear accelerators at each location.

**Table 1 T1:** Preliminary estimates of the number of events for the three main endpoints of interest, PSA relapse-free survival, overall survival and radiotherapy toxicity as defined from all sources.

Endpoint of interest	Approach used to estimate events	Events
PSA relapse-free survival	5-year endpoint, 10% event rate based on the trial, a randomised phase III multi-centre trial of Conventional or Hypofractionated High dose Intensity modulated radiotherapy for Prostate cancer, (CHHiP) ^46^ Sample size of 11 250 based on 75% attrition in this data (75% of 15 000)	1125
Overall survival	10-year endpoint, 29% event rate based the trial, a Randomised controlled Trial of high dose versus standard dose conformal radiotherapy for localised prostate cancer, (RT01)^11 46 49^ Sample size of 7500 based on 50% attrition in this data (50% of 15 000)	2175
Radiotherapy toxicity (all sources)	5-year endpoint, 12% event rate for ≥ grade 2 based on CHIIP trial high grade group^11 46 49^ Sample size of 10 000 based on much higher attrition of 60% attrition for this endpoint of interest (60% of 25 000=10 000 followed by 12% of 10 000)	1200

Estimates were based on data from NHS ISD, Scotland, Prostate Cancer Incidence.

PSA, prostate specific antigen.

Each of the five Scottish cancer centres involved in the study uses the same commercial database for storing information on patients receiving radiotherapy for prostate cancer. This database, known as ARIA, is supplied by Varian Medical Systems^20^ and is used to maintain a complete independent record of a patient’s treatment, which is required by law under the Ionising Radiation (Medical Exposure) Regulations 2017 .^21^ Separately, Public Health Scotland (PHS), Scotland’s national public health body, holds health and social care data for the entire Scottish population (5.4 million) as far back as the 1970s. Since this time, every NHS patient treated in Scotland has been allocated a unique identifier at birth, or on registering with Scottish healthcare services. This 10-digit numeric code, known as the Community Health Index number (CHI), is the primary mechanism for patient identification for every healthcare episode that happens in Scotland, making it straightforward to access and find information about an individual patient.

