#### Outcome measures

The primary outcome measures of the PROSECCA study are to establish what a patient’s probability of relapse-free survival, metastatic-free survival, cause-specific and overall survival will be when data from their EHR is combined with radiotherapy-specific parameters.

Secondary outcome measures include imaging-derived biomarkers and the independent and codependent predictive power of variables held within each patient’s EHR (online supplemental table 4) for prediction of primary outcomes.

Research and technical-scientific secondary outcomes include the curation of a population-based radiotherapy database containing imaging, dose and radiotherapy planning data and linked healthcare data from the national PHS archive. This also includes the establishment of a secure virtual environment, with high-performance computing capability, for rapid model development and outputs on the performance of a range of AI/ML models in predicting primary outcomes. Once established, this resource will also be used for future discovery research as well as validation of findings made by other researchers.

Patient-specific secondary outcomes will be in the form of a testbed for investigating the relationship between biochemical failure and radiotherapy-specific parameters such as dose, fractionation and planning techniques. This will also include how to personalise, or adapt, a patient’s course of radiotherapy by suggesting: the best form of therapy; the most appropriate dose and fractionation schedule; the optimal time to adapt; and the best mechanism for assessing any proposed personalised treatment. This will be available through an easy-to-use app.

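### Entry requires a PSA series recorded after radiotherapy, for every endpoint; this can select out early deaths and make overall survival look too favourable for men being assessed before treatment

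*Protocol article*

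**What the plan says.** Under Patient selection, the protocol article gives the entry rule for the whole study: "Patients must have had PSA recorded at regular intervals after radiotherapy, a radiotherapy planning CT and corresponding radiotherapy and healthcare data available". No number of tests, spacing or minimum duration is attached, and the rule is not limited to one endpoint. The exclusion sentence that follows removes palliative cases, "as well as those with no PSA information and follow-up healthcare and imaging data".

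Under Outcome measures, the primary outcomes are a patient's probabilities of "relapse-free survival, metastatic-free survival, cause-specific and overall survival will be when data from their EHR is combined with radiotherapy-specific parameters". The objectives, under the heading on predicting toxicity and tumour control, ask for "Medium (5 year) and long (10 year) estimates of three clinically significant endpoints". Of the predictive factors they say: "This information will be available both (1) prior to treatment and (2) during the course of treatment".

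The Study design section starts from about 25,000 treated patients and treats loss of data as a matter of numbers: "It has been assumed that 40% of data will be incomplete or not suitable for the endpoints" PSA relapse-free and overall survival, and 60% for toxicity. It concludes that enough complete data sets remain. Table 2 lists the national deaths data among the linked sources, together with inpatient, GP, out-of-hours and emergency records.

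**The concern.** The clock for the survival outcomes runs from radiotherapy, but entry depends on something observed later. A man who dies, moves away or becomes too frail to attend before a PSA series has built up may never qualify. His early death is then missing from the data, while the men who stay are credited with time in which, by construction, they could not have died. This is immortal-time selection.

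The planned use makes this matter. A clinician consulting the tool before treatment cannot know whether the patient will go on to have regular PSA tests. A model trained on men who did would describe a population that cannot be identified at the time of decision. The study also looks for new predictors in comorbidity and prescribing data. Those factors plausibly drive both early death and interrupted follow-up, so the rule may distort the associations that the study is meant to find. A larger cohort does not reduce a bias of this kind.

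**Working it through.** **The plan's own figures.** Table 1 and the Study design text reproduce exactly:
- Cohort: 25,000 × 0.60 = 15,000.
- PSA relapse-free survival: 15,000 × 0.75 × 0.10 = 1,125 events.
- Overall survival: 15,000 × 0.50 × 0.29 = 2,175 events.
- Toxicity: 25,000 × 0.40 × 0.12 = 1,200 events.

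The sums are in order; the issue is who is counted.

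**Inputs for the illustration.** Table 1 gives, for overall survival, "10-year endpoint, 29% event rate based the trial". Two assumptions are added, neither from the document: the hazard of death is constant from radiotherapy, and meeting the PSA condition requires a man to be alive and in follow-up at L years. L has to be assumed because the article does not define it.

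**Formulas.**
- Hazard: h = −ln(1 − 0.29)/10 = 0.0342 per year.
- Share dying before they can qualify: 1 − exp(−hL).
- Apparent 10-year mortality among those who qualify, counted from radiotherapy: 1 − exp(−h(10 − L)).
- Apparent 5-year mortality: 1 − exp(−h(5 − L)).

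**Results.**

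| L (years) | Die before qualifying | Apparent 10-year mortality | Apparent 5-year mortality | Deaths expected in 7,500 |
|---|---|---|---|---|
| 0 (no condition) | 0% | 29.0% | 15.7% | 2,175 |
| 0.5 | 1.7% | 27.8% | 14.3% | 2,083 |
| 1 | 3.4% | 26.5% | 12.8% | 1,989 |
| 2 | 6.6% | 24.0% | 9.8% | 1,797 |

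The understatement of 10-year mortality is 29.0 − 27.8 = 1.2 points at six months and 29.0 − 24.0 = 5.0 points at two years. At 5 years it is 15.7 − 14.3 = 1.4 points and 15.7 − 9.8 = 5.9 points. The absolute gap is slightly larger at the shorter horizon, where it falls on a lower mortality.

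**Does each endpoint need the rule?** Overall and cause-specific survival can be taken from the linked deaths data, and toxicity from the linked care records; none of these needs a PSA series. Table 1 already applies a different completeness assumption to each endpoint, whereas Patient selection applies the PSA condition to all patients.

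**The case against.** **The text does not say that an early death disqualifies a man.** With no minimum duration, a man tested on schedule who died at nine months could be read as having had PSA at regular intervals. The immortal period would then be only the time to the first tests; at three months the formula gives 28.4% against 29%. This stands as a limit on size. It does not remove the problem: some post-treatment PSA is required on any reading, and an undefined duration leaves entry to be settled after outcomes are known.

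**A reader might infer that every survival estimate is biased, and in the same direction.** The documents do not support that. Men who relapse early do have PSA values, and closely monitored men may be over-represented, so the direction for PSA relapse-free survival is open.

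**A reader might infer that follow-up imaging is also an entry condition.** The exclusion sentence is ambiguous: the word follow-up need not apply to imaging, and the list may mean lacking all the items or any one of them. The only imaging named for inclusion is the planning CT, a baseline item. The point rests on the inclusion sentence alone.

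**A reader might attribute the 40% and 60% losses to the PSA rule**, or set 25,000 × 0.50 × 0.29 = 3,625 deaths against the planned 2,175. Those percentages are feasibility assumptions covering all incomplete or unsuitable data, and the 25,000 are not restricted to radical intent. None of that gap can be assigned to the rule. How missing predictors are handled can be left to the full plan.

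**External validation on Hamlet-RT is planned and includes calibration.** It could reveal over-optimistic predictions, but it cannot restore the excluded men, and the article describes that study as directed at long-term side effects.

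**Conclusion.** The concern holds as a fault in the stated eligibility rule. Followed as written, the rule conditions the cohort on early survival and continued follow-up, while the outcomes are counted from radiotherapy and the predictions are intended for men not yet treated. Overall survival, and probably cause-specific survival, is exposed to estimates that are too favourable. Predictors tied to early death or loss to follow-up may be distorted. No direction can be given for PSA relapse-free survival.

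The size is unknown because the PSA requirement has no number or duration. The illustrated effect on 10-year mortality runs from about one percentage point if six months suffices to about five if two years are needed. It assumes a constant hazard and uses Table 1's 29%, which is itself borrowed from a trial.

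**What to change.** 1. Define eligibility only by what is known at the start of radiotherapy: radical-intent external beam treatment, a planning CT and record linkage.
2. Keep every such man for overall survival, cause-specific survival and toxicity, using the linked deaths and healthcare records.
3. Apply a PSA requirement only to the PSA relapse endpoint, and state it in numbers. Censor biochemical relapse at the last PSA; where the endpoint definition counts death as an event, still count linked deaths after the last PSA.
4. Tabulate baseline features and mortality for men with and without regular PSA, so that any remaining selection is visible.

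The cost is a change of protocol wording and some extra analysis, with no new data source. Some men will add little PSA information. The sponsor should check that the existing approval covers the added men: the abstract describes it as covering patients participating in the study, while the Consent section can be read more broadly. The Discussion reports that data access took from October 2022 to February 2025, so any need to extend the approval should be identified early.

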#### Consent

Access to unconsented health and social care data in Scotland is possible through a formal application to NHS Scotland Public Benefit and Privacy Panel for Health and Social Care (HSC-PBPP). Full permission to use electronic healthcare record data for all patients treated at the Scottish Cancer Centres participating in the study was granted by the HSC-PBPP panel on 1 July 2024. This is a national panel that considers the public benefit of every application and ensures that Information Governance (IG) standards align with the International Commissioner’s Office.^39^ Under article 6 (1)(e) of the General Data Protection Regulations (GDPR) the legal basis for the processing of the personal data used in the PROSECCA study is because it ‘*is necessary for the performance of the task carried out in the public interest*’.

#### Outcome measures

The primary outcome measures of the PROSECCA study are to establish what a patient’s probability of relapse-free survival, metastatic-free survival, cause-specific and overall survival will be when data from their EHR is combined with radiotherapy-specific parameters.

Secondary outcome measures include imaging-derived biomarkers and the independent and codependent predictive power of variables held within each patient’s EHR (online supplemental table 4) for prediction of primary outcomes.

Research and technical-scientific secondary outcomes include the curation of a population-based radiotherapy database containing imaging, dose and radiotherapy planning data and linked healthcare data from the national PHS archive. This also includes the establishment of a secure virtual environment, with high-performance computing capability, for rapid model development and outputs on the performance of a range of AI/ML models in predicting primary outcomes. Once established, this resource will also be used for future discovery research as well as validation of findings made by other researchers.

Patient-specific secondary outcomes will be in the form of a testbed for investigating the relationship between biochemical failure and radiotherapy-specific parameters such as dose, fractionation and planning techniques. This will also include how to personalise, or adapt, a patient’s course of radiotherapy by suggesting: the best form of therapy; the most appropriate dose and fractionation schedule; the optimal time to adapt; and the best mechanism for assessing any proposed personalised treatment. This will be available through an easy-to-use app.

